## Abstract

**Background:**

Up to 80% of breast cancer patients suffer from Cancer Related Cognitive Impairments (CRCI). Exercise is suggested as a potential supportive care option to reduce cognitive decline in cancer patients. This study will investigate the effects of a high-intensity interval endurance training (HIIT) on CRCI in breast cancer patients. Potentially underlying immunological and neurobiological mechanisms, as well as effects on patients’ self-perceived cognitive functioning and common cancer related side-effects, will be explored.

**Methods:**

A single-blinded randomized controlled trial will be carried out. The impact of HIIT on CRCI will be compared to that of a placebo-intervention (supervised myofascial release training). Both interventions will be conducted simultaneously with the patients’ first-line chemotherapy treatment typically lasting 12–18 weeks. Fifty-nine women with breast cancer will be included in each of the two groups. The study is powered to detect (α = .05, β = .2) a medium effect size difference between the two groups (d = .5) in terms of patients’ change in cognitive testing performances, from baseline until the end of the exercise-intervention. The cognitive test battery, recommended by the International Cancer and Cognition Task Force to assess CRCI, will be used as primary measure. This includes the Hopkins Verbal Learning Test (learning/verbal memory), the Controlled Oral Word Association Test (verbal fluency) and the Trail-Making-Test A/B (attention/set-switching). The following endpoints will be assessed as secondary measures: Go-/No-Go test performance (response inhibition), self-perceived cognitive functioning, serum levels of pro- and antiinflammatory markers (tumor necrosis factor alpha, Interleukin-6, Interleukin-1 alpha, Interleukin-1 beta, C-reactive protein, Interleukin-1 receptor antagonist and Interleukin-10), serum levels of neurotrophic and growth factors (brain-derived neurotrophic factor, insulin-like growth factor 1 and vascular endothelial growth factor), as well as common cancer-related side effects (decrease in physical capacity, fatigue, anxiety and depression, sleep disturbances, quality of life and chemotherapy compliance).

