### Sample size calculation

Sample size calculation was done to investigate the effect of exercise-intervention on the primary endpoint (objectively assessed cognitive performance using test battery of the ICCTF), in an analysis of covariance model (ANCOVA) using G*Power 3.1.9.2 software [87]. It was hypothesized that the changes in the test scores in the ICCTF test-battery, from baseline to after completion of the exercise-intervention, differ significantly between the HIIT group and the PCG-training group. Previous studies have shown that regular, low to moderate, exercise exerts rather small beneficial effects on CRCI in breast cancer patients [44–48]. However, pronounced effects of HIIT on fitness, cardiovascular health, fatigue and biomarkers have been reported in cancer patients [55–58]. Changes in these factors are discussed to play a pivotal role in the genesis of CRCI [24]. In accordance with it, we expect more meaningful effects of HIIT on CRCI compared to low to moderate exercise interventions. A medium effect of d = .5 was defined for sample size calculation. Alpha was set at 5%, but Bonferroni corrected due to multiple testing (4 outcome variables), leading to an adjusted alpha of 1.25%. Test power (1-β) was set at 80%. Participants’ test scores at baseline are included as covariate in the model. Required sample size in such an ANCOVA model can be calculated as (1-ρ^2^)*n, with ρ representing the correlation between participants’ baseline and post-treatment outcome-scores and n representing the sample size that would have been required, if a t-test of post-treatment outcome-scores was applied [88]. The correlation between patients’ test scores at baseline and at t_1_ was estimated with ρ = .6. This estimation was based on preliminary results (*N* = 40) of an ongoing trial of our group [89], indicating correlations between baseline and post-intervention measures of the applied tests of .6 and .8. Under the presuppositions made, the sample size calculation showed that 59 patients would be required in each group (*N* = 118). Based on attrition rate reported in existing studies applying HIIT in breast cancer patients during chemotherapy [49, 51] we accounted for 15% drop-out rate, leading to a total sample size of *N* = 136 patients.

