### Statistical analysis

An intention to treat (ITT) analysis will be performed We will also assess the effect of the complete treatment in a per protocol analysis. Separate 2 × 3 mixed ANCOVAs will be conducted to determine the effects of between-subjects factor exercise-intervention, within-subjects factor measurement time-point and their interaction on primary and secondary outcomes. Patients’ baseline scores of each specific parameter will be used as covariate. A significant main effect, of within-subjects factor measurement time-point, will be further investigated through Bonferroni corrected post hoc pairwise comparisons. Simple effects analyses will be conducted to determine potential group differences at each measurement time-point.

ANCOVA assumptions will be explored. In case of violations of normality assumption, appropriate nonparametric procedures will be used. In case of violations of ANCOVA assumptions of homogenous variances or sphericity, F-test will be adjusted. Eta-square values will be reported as effect size estimates for explained variance, and Cohen’s d values will be reported for post hoc pairwise comparisons.

In addition, an exploratory regression-based mediation analysis will be performed for each intervention induced change in biomarker expression. It will be tested if the change in biomarker expression, from baseline to completion of the exercise intervention, partially mediates the effect of the exercise intervention on the change in cognitive performance. The indirect effect, as combined effect of intervention induced change in biomarker and change in biomarker induced change in cognitive performance (i.e. the effect of mediation), will be calculated (product of regression coefficients). The 95% confidence intervals will be created around the indirect effect using bootstrapping [90, 91].

Statistical analysis will be performed by a statistician blinded to treatment groups. Statistical analyses will be conducted using SPSS 25® (IBM®, Armonk, NY, USA). For mediation analyses, the PROCESS custom dialog box (version 3.1, Model 4) for SPSS [91] will be used. A result will be considered significant at *p*-value equal to or less than .5 (in case of primary endpoint this will be adjusted to .0125).

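### The abstract gives the evaluable number (59 per group) as the number included and omits the Bonferroni step behind it; the planned 136 falls slightly short of 118 evaluable at 15% drop-out

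*Protocol article*

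**What the plan says.** The Methods part of the abstract gives the sample size as "Fifty-nine women with breast cancer will be included in each of the two groups" and continues: "The study is powered to detect (α = .05, β = .2) a medium effect size difference between the two groups (d = .5"). It mentions neither a multiplicity correction nor a drop-out allowance.

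The Sample size calculation section gives the full derivation. On alpha it says "Alpha was set at 5%, but Bonferroni corrected due to multiple testing (4 outcome variables), leading to an adjusted alpha of 1.25"%. On the effect it says "A medium effect of d = .5 was defined for sample size calculation". Power is 80%, the correlation between baseline and post-treatment scores is taken as ρ = .6, and the required number is (1 − ρ²) times the t-test sample size. The result is 59 required per group (N = 118). The section then says "we accounted for 15% drop-out rate, leading to a total sample size of" 136.

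The Statistical analysis section uses the same corrected level: "in case of primary endpoint this will be adjusted to .0125".

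**The concern.** Two things do not agree.

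- **Abstract against sample size section.** The abstract gives as the number included what the sample size section gives as the number required before drop-out. *Included* cannot easily be read as *evaluable*, because the Study population and recruitment section uses the same verb for entry into the study after written consent. The abstract therefore leaves out the 18 patients added for attrition (136 − 118). It also sets α = .05 next to a sample size that was calculated at .0125.
- **Within the sample size section.** The drop-out allowance appears to have been added to 118 (multiplying by 1.15) rather than solved for (dividing by .85). If so, the planned total does not leave the required number at the stated drop-out rate.

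At stake is whether the published recruitment number, alpha and power can be taken at face value. The abstract is the part most readers will use, and later reports will be compared with it.

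**Working it through.** **Inputs**, all from the Sample size calculation section unless noted: d = .5; power 80%; α = .05/4 = .0125 per test; ρ = .6, so 1 − ρ² = 1 − .36 = .64; drop-out 15%; required 59 per group (118); total 136. The abstract supplies α = .05 and 59 per group included. Sidedness is not stated. I assume two-sided tests, because a one-sided .0125 gives 78 × .64 = 49.9, or 50 per group, and only the two-sided test reproduces 59.

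**Step 1. Reproduce 59.** A two-sample t-test (noncentral t, two-sided .0125, 80% power, d = .5) needs 91 per group. Then 91 × .64 = 58.24, rounded up to **59 per group, N = 118**. As a cross-check, a direct ANCOVA F-test with one covariate and f = .25/.8 = .3125 also gives N = 118. The plan's figure is reproduced.

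**Step 2. The same formula at the alpha printed in the abstract.** At two-sided .05 the t-test needs 64 per group; 64 × .64 = 40.96, rounded up to **41 per group**. So 59 follows from .0125 per test and not from .05 per test.

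**Step 3. Reproduce 136.** 118 × 1.15 = 135.7, rounded up to **136**.

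**Step 4. What 136 delivers.**

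- Evaluable after 15% loss: 136 × .85 = 115.6, which is 2.4 below 118.
- Largest drop-out that still leaves 118: 1 − 118/136 = 13.2%.
- Number that would leave 118 after 15% loss: 118/.85 = 138.8, so 139, or 140 for two equal arms.

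**Step 5. Power.** ANCOVA with one covariate, two-sided α = .0125, standardised effect .5/√.64 = .625, noncentral t with N − 3 degrees of freedom:

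| Evaluable N | Power |
|---|---|
| 118 | 80.3% |
| 115.6 | 79.3% |
| 100 | 71.8% |

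The second row is the plan as written: 136 enrolled, 15% lost. The third is hypothetical: 118 enrolled as the abstract says, 15% lost (118 × .85 = 100.3).

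**The case against.** The strongest reply is that abstract and methods describe one design. They share d = .5, β = .2 and 59 per group, and .05 is the overall level that the sample size section itself names before dividing by four. That is right. A reader might infer that the abstract states a different trial, or a competing error rate; the documents do not support this. The abstract omits the correction, and the 41 per group arises only if .05 is taken as the per-test level, which the sample size and analysis sections both rule out.

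The shortfall is also small: 3 patients against 139, or 2.2%. The section takes the lower of the two preliminary correlations it reports, .6 and .8. With 115.6 evaluable, power would be about 89% at ρ = .7 and 97% at ρ = .8. This margin stands, and it is why no added recruitment is called for. It does not make the printed figures consistent with the plan's own ρ = .6.

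The 72% row needs someone to recruit from the abstract and ignore the stated total of 136. Nothing in the article shows that sites or the ethics commission would do so, so it only illustrates why the two numbers should not be confused.

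Finally, a reader might infer that, because the abstract speaks of change in performance, d = .5 is in change-score units and power is lower than claimed. The abstract assigns no standard deviation to d, and the sample size section fixes the calculation on post-treatment scores. With baseline as a covariate, the ANCOVA group effect is the same for change and post-treatment scores, so that inference fails.

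**Conclusion.** The point holds as a reporting and arithmetic correction of minor size. The abstract labels the required evaluable number as the number included, and it prints 59 per group beside α = .05 without the step to .0125 from which 59 comes. The planned 136 leaves about 116 rather than 118 at the stated 15% drop-out, which costs about one point of power (79.3% against 80.3%); 80% power holds up to about 13% drop-out.

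This rests on two-sided tests, d = .5, ρ = .6, and drop-outs providing no post-intervention score, as the plan's own allowance presumes. The derivation of 59 per group is sound on its stated inputs, and the design itself is not in question.

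**What to change.** **Abstract.** Replace the sample size and power statement with wording such as: *136 women will be randomised (68 per group); 59 evaluable per group are required for 80% power; α = .05 overall, .0125 for each of four tests.* This gives 59 as a requirement and does not claim that 136 will leave it at 15% drop-out.

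**Sample size calculation.** Keep 136 and the 15% assumption, and add that with 136 enrolled and 15% drop-out about 116 patients are evaluable and power is about 79%, with 80% power holding up to about 13% drop-out.

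**Cost.** Wording only, with no added recruitment and no change to the analysis. The stated power becomes slightly less favourable.

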**Discussion:**

This study will provide data on the question whether HIIT is an effective supportive therapy that alleviates CRCI in breast cancer patients. Moreover, the present study will help shed light on the underlying mechanisms of potential CRCI improving effects of exercise in breast cancer patients.

**Trial registration:**

DRKS.de, German Clinical Trials Register (DRKS), ID: DRKS00011390, Registered on 17 January 2018.

**Electronic supplementary material:**

The online version of this article (10.1186/s12885-018-4992-3) contains supplementary material, which is available to authorized users.

## Background

Up to 80% of breast cancer patients demonstrate a decrease in their cognitive capacity [1–5]. Most frequently reported are mild to moderate deficits in processing speed, attention, memory and executive functions (1–3, 5). In about 35% of affected patients, cognitive symptoms persist for months, or even years, after completion of medical treatments [6, 7], impairing daily functioning [8], limiting ability to return to work [9] and decreasing overall quality of life [8, 10–12]. Cognitive decline in breast cancer patients is mostly attributed to chemotherapy [13–15] leading to the expression of “Chemobrain” [16]. However, recent research shows that other factors, besides chemotherapy, can adversely impact cognition of breast cancer patients [17–23]. Consequently, the term “Cancer Related Cognitive Impairment” (CRCI) is currently preferred in the scientific literature [24, 25].

The underlying mechanisms of CRCI are still not fully understood. Recent findings indicate a key role of inflammatory pathways in the genesis of CRCI [26]. Affected patients show increased levels of proinflammatory markers, such as tumor necrosis factor alpha (TNF-α), Interleukin-6 (IL-6), Interleukin-1 Alpha (IL-1α), Interleukin-1 Beta (IL-1β) and C-reactive protein (CRP) [27–30]. At the same time, antiinflammatory cytokines, such as Interleukin-1 receptor antagonist (IL-1RA) and Interleukin-10 (IL-10) are decreased [30]. Hypothesized mechanisms of CRCI also include decreased levels of neurotrophic and growth factors, such as brain-derived neurotrophic factor (BDNF), insulin-like growth factor 1 (IGF-1) and vascular endothelial growth factor (VEGF) [31–35].

Research on therapeutic interventions alleviating CRCI in breast cancer patients is still scarce [25]. Recently, exercise increasingly gains attention as a potential supportive care option to reduce CRCI [24, 25, 36, 37]. In healthy elderly adults [38–40] and patients suffering from neurodegenerative diseases [41–43], there is substantial evidence that underlines the benefits of aerobic endurance training for functioning and structure of the central nervous system (CNS). However, initial studies, which are testing the effects of endurance exercise programs on CRCI in patients with breast cancer, show only small beneficial effects, if at all [44–48]. One reason could be that the applied training regimens, with low to moderate exercise intensities, were not intense enough to have meaningful effects on patients’ cognition. Moreover, recent research, in patients with breast cancer, shows that high-intensity endurance training is not only safe and feasible [49, 50], but is also more efficient than low to moderate endurance exercise, in terms of cognitive benefits [51]. The assumption, that higher intense exercise regimens have superior beneficial effects on CRCI, is supported by research demonstrating a positive dose-response relationship among exercise intensity and exercise induced anti-inflammatory effects/neurotrophin expression [52–54].

High-intensity interval endurance training (HIIT) seems to be an especially promising and time-efficient regimen, as potential supportive care option for CRCI, among the more intense exercise interventions. High-intensity interval endurance training increases peak aerobic fitness, it alleviates cardiovascular risk and fatigue in cancer patients [55, 56]. All the aforementioned are associated with CRCI [24]. HIIT increases anti-inflammatory markers [57] and neurotrophic factors [58], in a particularly effective and efficient way.

The main objective of this study will be to investigate the effects of a HIIT program on CRCI in breast cancer patients undergoing first-line chemotherapy, compared to a placebo-control group. The cognitive test battery, recommended by the International Cancer and Cognition Task Force to assess CRCI, will be used as primary measure [59]. The following endpoints will be assessed as secondary measures: Go-/No-Go-test performance (response inhibition), self-perceived cognitive performance, serum levels of pro- and antiinflammatory markers (TNF-α, IL-6, IL-1α, IL-1β, CRP, IL-1RA, IL-10), serum levels of neurotrophic and growth factors (BDNF, IGF-1, VEGF) as well as common cancer-related side effects (decrease in physical capacity, fatigue, anxiety and depression, sleep disturbances, quality of life and chemotherapy compliance).

## Methods

The present study is designed as a longitudinal randomized interventional study with two study arms. Participants will be allocated randomly to one of two forms of supervised exercise (see “Groups and interventions” section). Exercise will be done simultaneously with patients’ first-line chemotherapy regimen typically lasting 12–18 weeks (parallel group, single-blinded, randomized controlled trial (RCT)). That means that the exercise intervention will stop when chemotherapy stops. The pre-specified objectives and hypotheses are listed in Table 1. The study flowchart is shown in Fig 1. The study protocol was approved by the Ethics Commission of the Legal Department of the Hessen Regional Medical Council (Germany) (reference number: FF175/2016) and is registered at the WHO trial register (ID: DRKS00011390, see also Additional file 1). Any modifications to the protocol which may impact the implementation of the study, or impact any potential patient benefit, or may affect patient safety, including changes of study objectives, study design, patient population, sample sizes, study procedures, or significant administrative aspects, will require a formal amendment at the Ethics Commission. The project adheres to the declaration of Helsinki.

**Table 1 Tab1:** In- and exclusion criteria

Inclusion criteria	Exclusion criteria
• Initial diagnosis of mammary carcinoma stage I-IIIA • Female • Pending chemotherapy (neoadjuvant or adjuvant) • No contraindication to high-intense exercise	• Age < 18 years • History of former cancer diagnoses • Coronary Heart disease • Heart failure • Advanced lung disease • Major psychiatric disorders • Neurodegenerative disease • Cognitive dysfunction • Incapable to speak or understand German

**Fig. 1 Fig1:**
[figure not shown]
Flowchart of the trial. (1) Baseline measurement will be conducted shortly after diagnosis and 1–3 days before beginning of patients’ medical treatment; (2) Participants allocated to the high-intensity interval endurance training perform 3 × 3 min high-intensive intervals, interspersed by 90 s active rest-intervals during the first 8 weeks of their chemotherapy (duration ≈ 20–25 min). During the second half of participants’ chemotherapy, the number of intervals will be increased to 5 (duration ≈ 30–35 min); (2) Participants allocated to the Placebo Control Group receive a supervised myofascial release training program, inducing hardly any muscular effort and cardiovascular stimulation. Duration of sessions in the Placebo Control Group correspond to the duration of sessions in the high-intensity interval endurance training

### Study population and recruitment

Participants will be recruited at the Department for Oncology and Hematology of the Clinic Northwest and at the Department for Gynecology at the University Clinic in Frankfurt (Germany). Patients with initial diagnosis of mammary carcinoma stage I-IIIA and scheduled chemotherapy, not fulfilling any of the listed exclusion criteria in Table 2, will be recommended for study participation by the attending physician to the principal investigator. Patients will receive detailed descriptions of the study and will be given sufficient time to ask any questions. Patients will be included in the planned study only after they will give written informed consent. The participants will be included chronologically.

**Table 2 Tab2:** Objectives and hypotheses of the study

Objectives	Hypotheses
Main objective • To evaluate the effects of a HIIT versus placebo, conducted simultaneously with first-line chemotherapy regimen on CRCI, in women with breast cancer	Main hypothesis • In women with breast cancer, the decline in HVLT-R-, TMT-A/B- and COWAT test performance from baseline to completion of the exercise-intervention, is significantly smaller in the HIIT group compared to the control group (hypothesis A)
Secondary objective • To evaluate the effects of a HIIT versus placebo, conducted simultaneously with first-line chemotherapy regimen on self-perceived cognitive performance, in women with breast cancer	Secondary hypotheses • In women with breast cancer, the decline of FACT-COG scores from baseline to completion of the exercise-intervention/to 6-months follow-up^a^_,_ is significantly smaller in the HIIT group compared to the control group (hypothesis B)
• To evaluate the effects of a HIIT versus placebo, conducted simultaneously with first-line chemotherapy regimen on executive functioning subdomain response inhibition, in women with breast cancer	• In women with breast cancer, the decline of INHIB performance from baseline to completion of the exercise-intervention/to 6-months follow up, is significantly smaller in the HIIT group compared to the control group (hypothesis C)
• To evaluate the effects of a HIIT versus placebo, conducted simultaneously with first-line chemotherapy regimen on proinflammatory marker expression, in women with breast cancer	• In women with breast cancer, the increase of serum levels of TNF-α, IL-6, IL-1α, IL-1β, CRP from baseline to completion of the exercise-intervention/to 6-months follow up, is significantly smaller in the HIIT group compared to the control group (hypothesis D)
• To evaluate the effects of a HIIT versus placebo, conducted simultaneously with first-line chemotherapy regimen on antiinflammatory marker expression, in women with breast cancer	• In women with breast cancer, the decrease of serum levels of IL-1RA, IL-10 from baseline to completion of the exercise-intervention/to 6-months follow up, is significantly smaller in the HIIT group compared to the control group (hypothesis E)
• To evaluate the effects of a HIIT versus placebo, conducted simultaneously with first-line chemotherapy regimen on neurotrophin expression, in women with breast cancer	• In women with breast cancer, the decrease of BDNF serum level from baseline to completion of the exercise-intervention/to 6-months follow up, is significantly smaller in the HIIT group compared to the control group (hypothesis F)
• To evaluate the effects of a HIIT versus placebo, conducted simultaneously with first-line chemotherapy regimen on growth factor expression, in women with breast cancer	• In women with breast cancer, the decrease of VEGF and IGF-1 serum levels from baseline to completion of the exercise-intervention/to 6-months follow up, is significantly smaller in the HIIT group compared to the control group (hypothesis G)
• To evaluate the effects of a HIIT versus placebo, conducted simultaneously with first-line chemotherapy regimen on physical fitness, in women with breast cancer	• In women with breast cancer, the decrease of watts per kilogram and VO2_peak_ measured during IXT from baseline to completion of the exercise-intervention/to 6-months follow up, is significantly smaller in the HIIT group compared to the control group (hypothesis H)
• To evaluate the effects of a HIIT versus placebo, conducted simultaneously with first-line chemotherapy regimen on anxiety, fatigue, quality of life, sleep disturbances and chemotherapy compliance, in women with breast cancer	• In women with breast cancer, the change of HADS-D, MFI-20, EORTC-QLQ-C30, QOL-BR23 and PSQI scores from baseline to completion of the exercise-intervention/to 6-months follow up, is significantly more favorable in the HIIT group compared to the control group (hypothesis I)
• To evaluate the sustainability of the effects of a HIIT versus placebo conducted simultaneously with first-line chemotherapy regimen on CRCI in women with breast cancer	• In women with breast cancer, the decline in HVLT-R-, TMT-A/B- and COWAT test performance from baseline to 6-months follow up is significantly smaller in the HIIT group compared to the control group (hypothesis J)
Exploratory mediation analysis	
• To evaluate if the change in proinflammatory marker expression, from baseline to completion of the exercise-intervention, partially mediates the effect of the exercise intervention on the change of cognitive performance, from baseline to completion of the exercise-intervention, in women with breast cancer.	• In women with breast cancer, there is a significant indirect effect of exercise intervention on the change of HVLT-R−/TMT-A/B-/COWAT test performance, from baseline to completion of the exercise-intervention, through the change of TNF-α/IL-6/IL-1α/IL-1β/CRP serum level, from baseline to completion of the exercise-intervention (hypothesis K)
• To evaluate if the change in antiinflammatory marker expression, from baseline to completion of the exercise-intervention, partially mediates the effect of the exercise intervention on the change of cognitive performance, from baseline to completion of the exercise-intervention, in women with breast cancer.	• In women with breast cancer, there is a significant indirect effect of exercise intervention on the change of HVLT-R−/TMT-A/B-/COWAT test performance, from baseline to completion of the exercise-intervention, through the change of IL-1RA/IL-10 serum level, from baseline to completion of the exercise-intervention (hypothesis L)
• To evaluate if the change in neurotrophin marker expression, from baseline to completion of the exercise-intervention, partially mediates the effect of the exercise intervention on the change of cognitive performance, from baseline to completion of the exercise-intervention, in women with breast cancer.	• In women with breast cancer, there is a significant indirect effect of exercise intervention on the change of HVLT-R−/TMT-A/B-/COWAT test performance, from baseline to completion of the exercise-intervention, through the change of BDNF serum level, from baseline to completion of the exercise-intervention (hypothesis M)
• To evaluate if the change in growth factor marker expression, from baseline to completion of the exercise-intervention, partially mediates the effect of the exercise intervention on the change of cognitive performance, from baseline to completion of the exercise-intervention, in women with breast cancer.	• In women with breast cancer, there is a significant indirect effect of exercise intervention on the change of HVLT-R−/TMT-A/B-/COWAT test performance, from baseline to completion of the exercise-intervention, through the change of VEGF/IGF-1 serum level, from baseline to completion of the exercise-intervention (hypothesis N)

^a^ 6-month follow up will be conducted 6 months after completion of the exercise intervention

*HIIT* high-intensity interval endurance training, *HVLT-R* Hopkins Verbal Learning Test - Revised, *COWAT* Controlled Oral Word Association Test, *TMT-A/B* Trail Making Test part A/part B, *INHIB* Response Inhibition Test*, FACT-COG* Functional Assessment of Cancer Therapy – Cognitive function, *TNF-α* tumor necrosis factor alpha, *IL-6* Interleukin-6, *IL-1α* Interleukin-1 Alpha, *IL-1β* Interleukin-1 Beta, *CRP* C-reactive protein*, IL-1RA* Interleukin-1 receptor antagonist, *IL-10* Interleukin-10, *BDNF* brain-derived neurotrophic factor, *VEGF* vascular endothelial growth factor, *IGF-1* insulin-like growth factor 1, *VO2*_*peak*_ peak of oxygen uptake in milliliter oxygen uptake per kilogram bodyweight per minute, *IXT* incremental exercise test, *HADS-D* German version of the Hospital Anxiety and Depression Scale *MFI-20* The multidimensional Fatigue Inventory, *EORTC-QLQ-C30* core questionnaire 30 items of the European Organization for Research and Treatment of Cancer, *QOL-BR23* the breast cancer specific quality of life questionnaire of the EORTC *PSQI* Pittsburgh Sleeping Quality Index

